**Hypotheses**:

1. The combination of varenicline treatment plus tDCS to the left DLPFC will improve smoking cessation outcomes and relapse rates in treatment seeking smokers.
2. Active tDCS will reduce fMRI BOLD response to smoking cues compared to baseline within-subjects and compared to sham tDCS between subjects. Those who quit smoking in the last 4 weeks of treatment will show a “normalization” of brain reactivity to smoking cues and reward anticipation relative to those who were unable to remain abstinent over the short term due to tDCS extinguishing the salient properties of smoking-related cues and reward anticipation.
3. Compared to baseline, varenicline treatment will reduce within subject attentional bias, as measured by parameters of visual scanning behavior (VSB), to smoking and negative emotional cues.
4. Active tDCS will reduce attentional bias to smoking and negative emotional cues compared to sham tDCS. Those who quit smoking in the last 4 weeks of treatment will show “normalized” attentional bias patterns to smoking cues and reward anticipation relative to those who were unable to remain abstinent over the short term. Subjective measures of cravings will be correlated with within-subject changes in attentional bias to smoking cues and reward anticipation.
5. Individuals with larger changes in attentional bias to smoking-related cues and/or negative emotional cues, and lower measures of attentional bias to high-arousal/high-risk cues will have higher rates of abstinence (less relapse). Attentional bias will be measured by parameters of visual scanning behaviour and through the analysis of visual scanning patterns (sequences of fixations).
6. The probability of remaining abstinent over the long term will be inversely correlated with VSB measures of novelty seeking behavior.
7. Active tDCS will reduce impulsivity compared to sham tDCS as measured by higher delayed discounting scores.

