**Sample Size and Power Calculation**

If we assume a 40% abstinence rate at end of treatment in the varencline plus sham tDCS group, the abstinence rate in the active tDCS group would need to be double that or 80% in order to see a statistically significant difference with n=25 per arm, p <0.05, and 80% power. As such we do not expect to see a statistically significant difference between the two treatment arms at 25 subjects per arm.

For the treatment part of the study, the main purpose of the study is to establish an Effect Size for tDCS as an adjunct to standard varenicline treatment. This is independent of the number of subjects but allows us to estimate the N that would be required to achieve statistical significance depending on the effect size we observe. The effect size measure we will use will be the partial η2 generated by SPSS and is described in greater detail below.

For the MRI portion of the study, 15 to 25 subjects per group is standard in the neuroimaging field and is more than sufficient to detect significant within- and between-group differences in brain activity.

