**Data Analysis**

Continuous data (cravings, mood, cigarettes smoked/day, CO) will be assessed with 2 Gender x 2 (Laterality) x 10 (session) Analyses of Variance (ANOVA). Parallel ANOVAs will assess self-report measures during post-treatment follow-up. Categorical data (e.g., # abstinent participants/session) will be assessed with chi-square, and Kaplan-Meyer survival analysis for repeated measures. Planned comparisons will be performed for the critical experimental conditions (active tDCS) vs. sham.

The critical metric will be Effect Size (partial η2 generated by SPSS), rather than p level. This will reveal the degree of efficacy for the primary outcome variable, Consecutive Days Abstinent (small = .01, medium = .06, large = .14), and allow us to estimate N required to achieve statistical significance for this effect (80% power, α = .05, two-tailed). Pearson correlations will explore the possible relationship between effects of tDCS (session 10 scores, controlling for session 1) and trait factors (e.g., FTND, age, gender, depression).Analysis of MRI data

For the neuroimaging data, brain imaging measures will be compared between groups and across time points, using analysis of variance. MRI measures will also be related to subjective responses (i.e., baseline scores and changes in craving, mood, and withdrawal) using linear regression.

fMRI data will be analyzed by fitting a general linear model (GLM) to the data time-series at every voxel across the brain (and/or within ROIs) and assessing effects using F/t-tests and % signal change calculations. Quantitative T1 maps and DTI analysis will be analyzed at the whole brain level and using ROIs.

After back-sorting by treatment outcome (achieved/maintained abstinence), we expect baseline measures to predict relapse, and active tDCS treatment to result in more efficient functional activation, . than sham tDCS at the second MRI scan.

Analysis of Eye-Tracking Data

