For the eye-tracking data, gaze position data are processed by VAST into sequences of fixations and saccades and summary statistics of visual scanning parameters are computed. The VAST parameters include: the number of fixations, the average fixation duration, the average saccadic amplitude and the number of transitions for each image type. These parameters are sensitive measures of attentional bias for different visual cues. The outcome measures of this paradigm will be analyzed using a mixed-model analysis of variance (ANOVA). The within-groups factors are the image types (smoking, neutral, high valence) and session (sessions 1, 2, 3,4 and 5) and the between-groups factor is group (active tDCS and sham tDCS). Pearson’s product–moment correlations will be conducted between parameters of attentional bias and subjective craving scores. Through analysis, we will investigate and compare the treatment effects of varenicline and active tDCS on attentional bias in different sessions. We will also examine the relationship between changes in attentional bias and craving.

By means of a mixed design repeated-measures ANOVA, the VAST parameters will be compared within-subjects at 5 sessions to investigate the effects of varenicline treatment. The parameters will also be compared between the two groups of subjects to examine the treatment effects of active tDCS. We will also compare the VSB parameters of those who quit smoking in the last 4 weeks of treatment and those who were unable to remain abstinent to find out the possible indicators of treatment outcome. Pearson correlation method will be used to explore the relationships between: a) subjective craving and VSB parameters, b) sensation seeking behavior as measured by the sensation seeking scale measures and VSB parameters. Also we will use recurrent neural networks (Chung et al, 2018) to analyze differences between fixation sequences of patients that were treated with tDCS and patients that were not, and between patients that quit smoking and those that were not. Using Cox regression of survival analysis, we will also investigate the correlation between the length of abstinence (time to relapse) and VSB parameters associated with smoking cues, negative emotional cues and high-arousal/high-risk cues.

All data analysis will be conducted using SPSS, SPM or R as appropriate.

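### No treatment-arm term is named for the Cox or quitter-versus-non-quitter gaze analyses, so for post-baseline gaze an apparent predictor of abstinence may only mark who received active tDCS

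*Protocol*

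**What the plan says.** All of this is in the Protocol.

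- **Data Analysis, eye-tracking part, ANOVA.** The mixed-model ANOVA has image type and session as within-subject factors, and "the between-groups factor is group (active tDCS and sham tDCS").
- **Same part, outcome comparison.** "We will also compare the VSB parameters of those who quit smoking in the last 4 weeks of treatment and those who were unable" (that is, participants who did not stay off cigarettes). The two groups are defined by smoking outcome alone.
- **Same part, survival model.** "Using Cox regression of survival analysis, we will also investigate the correlation between the length of abstinence (time to relapse) and VSB parameters" for the three cue types. No other model term is named, and the session that supplies the gaze values is not given.
- **Hypothesis 1.** "The combination of varenicline treatment plus tDCS to the left DLPFC will improve smoking cessation outcomes and relapse rates in treatment seeking smokers".
- **Hypothesis 4.** "Active tDCS will reduce attentional bias to smoking and negative emotional cues compared to sham tDCS".
- **Hypothesis 5.** "Individuals with larger changes in attentional bias to smoking-related cues and/or negative emotional cues" are expected to be abstinent more often. The Eye Tracking section likewise asks whether within-subject change in visual scanning behaviour (VSB) predicts cessation and long-term abstinence.

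**The concern.** Hypotheses 1 and 4 together make randomised arm a cause of both variables that hypothesis 5 relates. If tDCS works as hoped, quitters contain more active-arm participants than non-quitters do, and active-arm participants have larger gaze changes. A comparison that ignores arm then finds larger gaze change among quitters, even if gaze change says nothing about who quits within either arm.

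What is at stake is the reading of hypothesis 5 and of the Eye Tracking questions about gaze change and abstinence. The stronger the effect of tDCS on both variables, the more easily a marker of assignment could be reported as a gaze predictor of cessation. The text names group for the adjacent ANOVA, and elsewhere in Data Analysis it names an adjustment for session 1 scores. A reader following it as written would therefore have no prompt to add arm to these two analyses.

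**Working it through.** **The protocol's own figure.** Sample Size and Power Calculation: "If we assume a 40% abstinence rate at end of treatment in the varencline plus sham tDCS group", 80% is needed in the active group with 25 per arm and 80% power. By the pooled normal formula, with mean proportion 0.6:

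z = (0.4 × √25 − 1.96 × √(2 × 0.6 × 0.4)) / √(0.4 × 0.6 + 0.8 × 0.2) = (2.000 − 1.358) / 0.632 = 1.015, so power is 84.5%.

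Fisher's exact test gives 78.8%. The stated figure reproduces. No design figure is given for the gaze analyses.

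**Inputs for the check.** From the protocol: 25 per arm and 40% sham abstinence; 80% active abstinence appears there only as the rate needed for significance. Assumed: gaze change is normal with SD 1, shifted by d = 0.5 to 1.0 SD in the active arm; active abstinence of 50% or 60% as smaller effects; relapse hazard ratios (HR) of 0.6 and 0.4; 25% of sham relapse-free at week 26. In every case gaze is unrelated to abstinence within arm, so a significant result is an artefact of arm.

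**Quitter comparison, one case by hand** (40% vs 80%, d = 1.0).
1. Expected quitters: 10 sham + 20 active = 30, of whom 20/30 = 0.667 are active.
2. Expected non-quitters: 15 sham + 5 active = 20, of whom 5/20 = 0.25 are active.
3. Spurious mean difference: d × (0.667 − 0.25) = 0.417 SD. Simulation gives 0.418.
4. Variance within outcome group is 1 + d² × share × (1 − share): 1.222 for quitters and 1.188 for non-quitters, pooled 1.208.
5. SE = √(1.208 × (1/30 + 1/20)) = 0.317, so z = 0.417 / 0.317 = 1.31.
6. Rejection probability: Φ(1.31 − 1.96) + Φ(−1.31 − 1.96) ≈ 26%. Simulation gives 25.1%.

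**Quitter comparison, simulated (2,000 runs per cell).**

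| Sham vs active abstinent | d | No arm term | Hand approximation | With arm |
|---|---|---|---|---|
| 40% vs 60% | 0.5 | 6.6% | 6.4% | 4.8% |
| 40% vs 60% | 0.8 | 7.6% | 8.2% | 4.6% |
| 40% vs 60% | 1.0 | 8.3% | 9.7% | 5.4% |
| 40% vs 80% | 0.5 | 10.1% | 10.8% | 4.8% |
| 40% vs 80% | 0.8 | 18.8% | 19.2% | 4.8% |
| 40% vs 80% | 1.0 | 25.1% | 25.9% | 4.5% |

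At 40% vs 50% the rate without arm is 5.1% to 5.9%. At 40% vs 40%, or with d = 0, it is about 5%.

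**Cox model, score test (6,000 runs per cell; sham 25% relapse-free).**

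| Relapse HR | d = 0.5 | d = 0.8 | d = 1.0 |
|---|---|---|---|
| 0.6, no arm | 6.2% | 8.6% | 10.0% |
| 0.4, no arm | 9.5% | 14.6% | 19.2% |

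Stratified by arm, the rate is 4.6% to 5.8%. A repeat with fresh random numbers gave 6.8%, 8.6% and 9.8% at HR 0.6, and 9.5%, 15.2% and 20.4% at HR 0.4, with 5.2% to 5.7% when stratified. Monte Carlo error at 10% is 1.96 × √(0.1 × 0.9 / 6000) = 0.8 points, hence an upper end of about 11% for the moderate case. With 40% of sham relapse-free and HR 0.56 (40% vs 60% relapse-free), 600 runs gave 6.2% at d = 0.5 and 8.3% at d = 0.8. In the latter cell the spurious hazard ratio was about 0.91 per SD of gaze change.

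**The case against.** **Silence is not exclusion.** The text does not say that the arms are pooled or that arm is left out. Covariates of an exploratory Cox model are often left to a statistical analysis plan, which is not at hand. A reader might infer that the protocol prescribes a pooled, unadjusted model; it does not. What stands is narrower: two analyses are described without arm, next to one that names it, on variables that the protocol expects arm to change.

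**Baseline gaze is safe.** It precedes treatment and is independent of arm by randomisation, apart from chance imbalance. A Cox model on baseline VSB would not be affected. This objection stands and limits the point to on-treatment values and change scores.

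**The association may be real.** If tDCS promotes abstinence by changing gaze, the unadjusted association includes that pathway, and the simulated null excludes it by construction. Adjusted and unadjusted models answer different questions. This stands as a reason to keep the unadjusted result as supplementary. It does not make that result evidence that gaze predicts abstinence among people treated alike.

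**The large figures need large effects.** The protocol gives no tDCS effect on gaze. It offers 80% active abstinence as what significance would require, and says a significant difference is not expected. This stands: 25% is the upper end of the range, not a forecast.

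**The MRI analyses.** A reader might extend the point to them, for instance to the plan that "MRI measures will also be related to subjective responses". The documents do not support that extension. That regression concerns craving, mood and withdrawal rather than abstinence, and was not part of the check. The Background also plans to examine quitters and non-quitters within the sham group for both fMRI tasks.

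**Conclusion.** The point holds for post-baseline VSB values and changes in the quitter comparison and the Cox regression. Under gaze shifts of 0.5 to 1.0 SD and no within-arm association, the error rate at nominal 5% is about 6% to 11% for moderate effects on abstinence (relapse HR 0.6, or 40% vs 60% abstinent). It is about 9% to 25% for large effects (HR 0.4, or 40% vs 80%). Including or stratifying by arm returns it to about 5%. There is no inflation if tDCS affects only gaze or only abstinence, and almost none at 40% vs 50%.

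The gaze shifts, hazard ratios and week-26 relapse-free rate are assumptions. The 40% sham rate is the protocol's. These are secondary analyses in a 50-person pilot. The primary comparison is untouched, and the ANOVA that tests the tDCS effect on gaze already includes group. The change is still worth making, because gaze change as a predictor of abstinence is a stated hypothesis and the remedy is almost free.

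**What to change.** In the eye-tracking part of Data Analysis:

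1. State for each of the two analyses which gaze values are used: baseline, a named on-treatment session, or change from baseline.
2. For post-baseline values, stratify the Cox regression by treatment arm.
3. For post-baseline values, include arm as a term in the quitter-versus-non-quitter comparison.
4. Report the unadjusted result as supplementary, and say that it may include mediation through treatment.

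The cost is one term or stratum per model and a sentence or two of text. No new data or visits are needed.
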